	-Percentage of population living in area in most deprived quintile -Long-term unemployment (jobseekers claimant > 12 months)	-Scottish index of Multiple Deprivation score (average score across data zones for each local authority)
Population/outlet density	-Population density per square kilometre	-Estimated mid-year population -Population density per square kilometre -On-licence density -Off-licence density
	-On-licence density	
	-Off-licence density	
Alcohol-related harm	-Alcohol-related hospital admissions (standardised rate; narrow measure) -Alcohol-related violent crime	-Alcohol-related hospital admissions (standardised rate)
Demographic variables	-Median age	-Median age

Potential variables for inclusion in the matching processes were identified using a modified Delphi approach [67]. Matching variable selection was refined following an evaluation of covariate balance from initial propensity score matching analyses (presented at ExILEnS team meeting 22.09.17), and discussion with members of the ExILEnS team ([name], [name], [name] and [name]). All of the covariates included in the matching process were measured at baseline (2009–2011).

Table 2 lists the final covariate set which will be used for matching for English and Scottish local authority areas. The covariate list differed between the two countries due to differences in the publicly available data at local authority level.

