### Power calculations

No quantitative data is available on the effect of public health engagement in licensing on alcohol-related harms. The assumed mechanism by which such engagement might reduce harms however, is by influencing the local licensing system. Statistical power estimations therefore have been based on effect sizes from two recent studies of the effect of alcohol premises licensing on alcohol-related hospital admissions and reported crime rates at the level of ‘lower tier local authority’ (LTLA) in England [28, 29]. Areas with active alcohol licensing policies had an average additional 2% (95% CI -3%:-2%) annual reduction in alcohol-related hospital admissions in the period up to and including 2013 compared to those without such policies [28]. Similarly, for the period up to 2013, an additional 4–6% annual decrease was seen in alcohol-related violent crimes, sexual crimes and public order offences in areas with active licensing policies compared to those with none [29].

We used the methodology developed by Edland for power calculations of linear mixed effects models with random slope [68]. Based on the previous studies, we conducted separate sample size calculations for alcohol-related hospital admissions and reported crime rates. For both analyses we assumed a standard level of statistical significance α (5%) and statistical power β (80%), and further assumed a 9-year follow-up (2009–2018) and a two-sided alternative. Table 4 outlines the detectable effect size with 20 intervention and 20 control areas.

**Table 4 Tab4:** Sample size data

	Expected average effect size %/year (slope)	Between-slope variance	Residual variance model	Number of areas in each group
*From previous study of impact of licensing on alcohol-related crime* [29]				
Crime rates^a^	−4.00% (−0.04)	0.003	0.03	29
	−5.00% (−0.04)	0.003	0.03	19
	−6.00% (−0.06)	0.003	0.03	13
*From previous study of impact of licensing on alcohol-related hospital admissions* [28]				
Rates	−2.31% (−0.229)	0.110	0.011	34
*Current study - minimum detectable effect size with proposed sample size*				
20 areas per group	−3.00% (−0.296)	0.110	0.011	20

^a^Effect size is a range between 4 and 6% as estimated by d Vocht et al. (2016) using quadratic trends

Based on Table 4, we expect the study to be able to detect effects on our outcomes within the range found in previous observational studies with 20 intervention and 20 control areas.

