The first draft of each measure will define dimensions and indicators for different categories of PHT or licensing activity and will be developed based on current research literature and published best practice guidance. This draft will be used to code data a subset of interventions areas, and then all intervention areas, revising as needed at each stage. The resulting measure will be sent to UK-based public health and licensing experts, to review for clarity, completeness and relevance and then further revised based on their feedback. The range of practice for each included indicator of intensity will be analysed by each researcher, and discussed and combined to develop a single measure and defined grading scales for each included indicator. This version will then be applied independently by two researchers to a subset of intervention and control area data, and the resulting scores compared in discussion, checking for consistency and face validity. The final stage of development will involve deciding, using our data, and in consultation with experts, whether and how different dimensions or indicators within the measure should be weighted. Weightings will also be informed by parallel work by the team to further develop a theory of change for PHT involvement in licensing.

Once the measures have been finalised using this iterative process, they will be reapplied to the data for all intervention and control areas to calculate intensity scores for each 6 month period April 2012 to March 2019. Two researchers will apply the measure to 10% of areas (*n* = 4) to examine inter-rater reliability. Where identified, discrepancies will be discussed and assessed by a third reviewer as needed. The scoring system will then be revised and another 4 areas assessed by two reviewers. In the event of further serious discrepancies, this process will be repeated. We will report the inter-rater reliability of the finalised measure.

The agreed intensity scores will be used to examine the relationship between intervention intensity, licensing regime activity and alcohol-harm outcomes.

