### Analysis of primary outcomes

We will evaluate temporal trends in all key outcomes from 2009 to 2018 and compare these in intervention and control areas using hierarchical log-rate growth models. This method was previously used by members of the research team to investigate the association between a metric of ‘licensing activity’ and alcohol related hospital admissions [28, 30] and crime rates [29] in England.

An additional feature of this study over and above those studies, is the chunking of the intervention intensity measure into 6-month intervals enabling specific exploration of causal effects through inclusion of pre/post indicators and interactions in the growth models as well as the use of ‘Differences-in-Differences’ statistical methods [77]. Inferences about causality can be made through quantitatively evaluating, using a pre-specified plan based on the emergent theory of change, whether there is statistical evidence of changes in longitudinal trends in outcome measures that coincide with the expected effect of the intervention (and is not present in the corresponding control area). Where data is available we will analyse outcomes by deprivation and gender.

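### The power calculation counts the 2009–2011 baseline years as follow-up, so the stated 3.00%/year detectable effect does not describe an effect that starts in 2012

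*Protocol article*

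**What the plan says.** The Power calculations section of the protocol article uses the "methodology developed by Edland for power calculations of linear mixed effects models with random slope" and "further assumed a 9-year follow-up (2009–2018) and a two-sided alternative". Table 4 gives the "detectable effect size with 20 intervention and 20 control areas": for admissions, −3.00%/year (slope −0.296). The section closes by expecting that effects within the previously reported range can be detected.

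Other sections divide the same calendar period differently:

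- Control areas: "All of the covariates included in the matching process were measured at baseline (2009–2011").
- Study aim: engagement is assessed from 2012 to 2018.
- Data collection: the team will "calculate intensity scores for each 6 month period April 2012 to March 2019".
- Analysis of primary outcomes: "We will evaluate temporal trends in all key outcomes from 2009 to 2018 and compare these in intervention and control areas". The next paragraph adds pre/post indicators and interactions in the growth models, and difference-in-differences. It bases causal inference on trend changes that coincide with the intervention's expected effect and are absent in the control area.

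**The concern.** The article treats the same three years as baseline in one section and as follow-up in another. The power model has one slope difference per group comparison, so it assumes that the two groups diverge from 2009. If divergence begins with engagement in 2012, a single slope fitted over 2009–2018 picks up only part of it. The matching covariates in Table 2 are levels rather than prior trends, so a pre-existing slope difference would also enter such a whole-period comparison.

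At stake is the reading of a null result, which the Discussion says may matter as much for policy as a positive one. A reader who takes 3.00%/year at 80% power at face value would credit a null finding with more sensitivity to a post-2012 effect than a whole-period slope comparison would have.

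**Working it through.** **Inputs.** Power calculations and Table 4: two-sided 5%, 80% power, 20 areas per group. Admissions: slope 0.296 (3.00%/year), between-slope variance 0.110, residual variance 0.011. Cited admissions effect: −2%/year, interval −3% to −2%. Ten annual points 2009–2018 (t = 0 to 9) give S = Σ(t − mean)² = 82.5.

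**1. Reproduce the stated figure.** Random-slope formula, normal approximation:

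n per group = 2(1.96 + 0.8416)² × [between-slope variance + residual variance/S] / slope²

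= 15.70 × (0.110 + 0.011/82.5) / 0.296² = 19.7, so 20, as stated. For slope 0.229 the formula gives 33.0, against a printed 34.

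**2. Does the number of years matter?** For 2012–2018 alone (7 points, S = 28): 15.70 × (0.110 + 0.011/28) / 0.296² = 19.8, still 20. Between-slope variance dominates, so dropping three years leaves the admissions figure unchanged.

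**3. Dilution of a later-starting effect.** Take a group difference of zero before onset and linear after it. The fraction recovered by one least-squares slope over 2009–2018 is Sxy/S:

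- divergence first visible in 2012: 70/82.5 = 0.85
- kink at 2012, divergence first visible in 2013: 59.5/82.5 = 0.72

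**4. Consequences for admissions.** The standard error of the slope difference at 20 per group is √(2 × 0.110133/20) = 0.105.

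| Fraction recovered | Detectable effect | Power for 3%/year | n per group for 3%/year |
|---|---|---|---|
| 1 (as planned) | 3.00%/year | Φ(2.82 − 1.96) = 80% | 20 |
| 0.85 | 3.00/0.848 = 3.5%/year | Φ(2.39 − 1.96) = 67% | 19.7/0.848² = 27.4, so 28 |
| 0.72 | 3.00/0.721 = 4.2%/year | Φ(2.03 − 1.96) = 53% | 19.7/0.721² = 37.9, so 38 |

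An assumed one-year lag added to the last row gives 47.5/82.5 = 0.58, about 5.2%/year and 37% power. Quarterly points with a kink in January or April 2012 and no lag give fractions of about 0.74–0.78, inside the range shown.

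**5. The pre/post contrast.** Its sensitivity cannot be worked out from the article, because it depends on how area slopes vary. For slope 0.296 and a kink at 2012:

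- Each area's slope constant apart from the effect: the 0.110 cancels. The variation in the kink term left after adjusting for linear time is 46.9 − 59.5²/82.5 = 3.99, so n = 15.70 × (0.011/3.99)/0.296², below 1 per group.
- Slopes vary only after onset: n is about 20.
- Pre- and post-slopes vary independently, 0.110 each, residual term ignored: 15.70 × 0.220/0.296² = 39.4.

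**The case against.** The strongest reply is that the remedy is largely in the plan already. Analysis of primary outcomes commits to pre/post terms and difference-in-differences under a pre-specified plan. Its remark about an additional feature compares this study with the earlier studies; it does not rank those terms as secondary. This stands. A reader might infer that the whole primary analysis is diluted, or that baseline trend differences go unadjusted, and the article supports neither. What remains is that the power calculation contains no such term, so its figure belongs to a different contrast.

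A reader might also infer that counting three extra years itself inflates the stated power. For admissions it does not (step 2).

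The borrowed effects may already be whole-period averages: the Background reports the earlier admissions result over 2009 to 2015. Table 4 is then coherent on its own scale, but 3.00% is still not a post-2012 effect. Nor is 2009–2011 cleanly unexposed everywhere. Scottish health boards gained their role under the 2005 Act, which touches 6 of the 20 pairs, and English Directors of Public Health gained theirs in 2011.

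For crime, a firm claim that the detectable effect leaves the cited 4–6% range is not supported. The printed crime sample sizes (29, 19, 13) do not follow from the printed variances with annual points (33.0, 21.1, 14.7, so 34, 22, 15). They do follow with the residual term near zero (29.4, 18.8, 13.1). At 20 per group the diluted crime effect is about 5.7–6.7%/year without the residual term (4.85/0.848 to 4.85/0.721) and 6.1–7.1%/year with it (5.14/0.848 to 5.14/0.721), so the answer turns on which was used.

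**Conclusion.** The point holds for the power statement. The calculation labels the protocol's own baseline years as follow-up and powers a slope difference present from 2009, so 3.00%/year at 80% power does not describe an effect starting in 2012. If one 2009–2018 slope is compared, the detectable admissions effect is about 3.5–4.2%/year and power for 3%/year about 53–67%. That range lies outside the cited −3% to −2% interval, so on this reading the closing claim about previously reported effects is unsupported for admissions.

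These sizes assume annual points, linear growth of the effect, no lag and no exposure before 2012. A lag lowers sensitivity; earlier exposure in Scottish areas would lessen the dilution. If the pre/post contrast carries the inference, the direction of the error is not determined by the article, but the stated figure still does not apply to it.

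**What to change.** In Power calculations, label 2009–2011 as the pre-period. Redo the calculation for the change-in-slope or difference-in-differences contrast already planned in Analysis of primary outcomes. State the assumed onset, the lag, and how area slopes vary before and after onset, and give the detectable effect as a range over those assumptions. Name that contrast as the main estimate and present the whole-period slope comparison as descriptive. Revise the closing sentence on detectable effects to match.

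The cost is a re-run calculation and some wording; the outcome series planned from 2009 already supply the pre-period. The stated sensitivity may become less favourable, by an amount that depends on the assumed variance structure and on any earlier exposure in the Scottish areas.

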As public health engagement in this area is potentially resource-intensive, findings from ExILEns will inform decisions on about whether this activity represents the best use of time for public health teams. If it is shown that there are measurable benefits, this will help to make the case for greater investment in public health capacity and/or potentially greater legislative support through the introduction of a public health objective in England. If, however, our findings suggest limited effects of public health activity in this arena, or little potential for licensing policy to materially affect alcohol-related harms, then this will contribute to current debate around more substantial legislative changes [84]. Should this study have null findings, this may, therefore, be as significant in policy terms as a demonstration of positive effects.

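### Table 4 supports the power conclusion only at the favourable end of each prior range: 20 areas per group give about 57–59% power at the prior admissions effect and 57–64% at a 4% crime effect

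*Protocol article*

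**What the plan says.** The Power calculations section borrows its effect sizes from two earlier studies of licensing policy. For admissions: "Areas with active alcohol licensing policies had an average additional 2% (95% CI -3%:-2%) annual reduction in alcohol-related hospital admissions". For violent, sexual and public order offences it gives an additional decrease of 4–6% per year. Significance is set at 5% and power at 80%, and the authors "further assumed a 9-year follow-up (2009–2018) and a two-sided alternative". On method: "We used the methodology developed by Edland for power calculations of linear mixed effects models with random slope".

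Table 4 then lists the areas needed per group: 29, 19 and 13 for crime effects of 4%, 5% and 6% per year, and 34 for the prior admissions effect of 2.31% per year. A last row gives 3.00% per year as the minimum detectable effect with 20 areas per group, using the admissions variances.

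The section closes, on the strength of Table 4, with: "we expect the study to be able to detect effects on our outcomes within the range found in previous observational studies". The Discussion later adds: "Should this study have null findings, this may, therefore, be as significant in policy terms as a demonstration of positive effects".

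**The concern.** The closing sentence carries no qualification and covers the outcomes generally, so a reader will take it that effects of the size seen before are covered at 80% power. The rows just above it show otherwise for the prior admissions effect (34 needed, 20 available) and for the lowest crime effect (29 needed, 20 available).

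What is at stake is how a non-significant result will be read. If the true admissions effect equals the prior estimate, such a result is not much less likely than a significant one. The article also expects effects on A&E attendances to be in or around the crime range, so the shortfall at the low end of that range bears on that outcome too. No variances are given for A&E, so its power cannot be computed.

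**Working it through.** **Inputs, all from the Power calculations section and Table 4.** Two-sided 5% (z = 1.96); 80% power (z = 0.8416; sum 2.8016, square 7.849); 20 areas per group. Crime: slope variance 0.003, residual variance 0.03. Admissions: slope variance 0.110, residual variance 0.011, slope 0.229 for 2.31%/year.

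**Formula.** For a random-slope model, n per group = 2 × 7.849 × V / δ², where V = slope variance + residual variance / S and S is the sum of squared deviations of the time points from their mean. The article does not give the number of time points used, so several schedules are shown. S = 82.5 for 10 annual points, 60 for 9 annual points, and about 264 to 333 for 37 to 40 quarterly points.

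**Step 1: reproduce Table 4.**
- Admissions, 10 annual points: V = 0.110 + 0.011/82.5 = 0.1101. Then n = 15.698 × 0.1101 / 0.229² = 33.0, or 34 with the noncentral t. Table 4 has 34. The minimum detectable slope is √(15.698 × 0.1101 / 20) = 0.294; Table 4 has 0.296. The schedule hardly matters because the residual term is tiny.
- Crime, slope variance only: n = 15.698 × 0.003 / δ² = 29.4, 18.8 and 13.1 for slopes of 0.04, 0.05 and 0.06. Table 4 has 29, 19 and 13. Quarterly data give 30.3–30.6, 19.4–19.6 and 13.5–13.6. Annual data give about 33–34, 21–22 and 15.
- The 5% crime row prints a slope of −0.04, but n = 19 needs −0.05 (0.04 gives 29.4). This looks like a misprint and does not affect the point.

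**Step 2: power with 20 per group, scaled from Table 4's own sample sizes.** Power = Φ(2.8016 × √(20/n) − 1.96).
- Admissions 2.31%/year: Φ(2.8016 × √(20/34) − 1.96) = Φ(0.189) = 0.575.
- Admissions 2%/year: Φ(2.8016 × √(20/34) × 2/2.31 − 1.96) = Φ(−0.100) = 0.460.
- Crime 4%/year: Φ(2.8016 × √(20/29) − 1.96) = Φ(0.367) = 0.643.

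**Step 3: the same from the printed variances.** Power = Φ(δ / √(2V/20) − 1.96).
- Admissions: 0.588 at 2.31%/year (0.57 with the noncentral t) and 0.472 at 2%/year.
- Crime, by schedule:

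| Schedule assumed | Power at 4%/year | Effect with 80% power |
|---|---|---|
| Slope variance only | 0.637 | 4.85% |
| Quarterly, 37–40 points | 0.621–0.624 | 4.92–4.94% |
| Annual, 10 points | 0.587 | 5.14% |
| Annual, 9 points | 0.571 | 5.24% |

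The noncentral t lowers each of these crime powers by about 0.02.

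**Step 4: 80% thresholds from Table 4's own sample sizes.** Admissions: 2.31% × √(34/20) = 3.01%/year. Crime: 4% × √(29/20) = 4.82%/year.

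**The case against.** The best defence is that the sentence claims only that effects within the prior range are detectable, which need not mean all of them or the point estimate. On that reading Table 4 agrees: crime effects of 5% and 6% need 19 and 13 areas, and 3.00% lies on the limit of the admissions interval. The unfavourable rows are also printed directly above, so nothing is hidden. This rules out any charge that Table 4 is miscalculated. It does not rescue the sentence, which is unqualified and true at 80% power only for the larger effects in each range.

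Four stronger readings are tempting, and the documents do not support them.
- A reader might infer that the study cannot detect the prior effects at all. It can, but with less than 80% power.
- A reader might infer that the prior effects are an upper bound for public health engagement, since it is assumed to act through licensing. The article does not show this. It selects areas with sustained high engagement, and its list of intervention components includes direct work with licensees, which need not pass through licensing policy.
- A reader might infer that the Discussion claims a null result is statistically as informative as a positive one. The sentence is hedged and speaks of policy relevance.
- A reader might want a fixed rule, such as accepting no effect only if the interval excludes a 2%/year reduction. The plan gives no such margin. A threshold of 3.00% implies a standard error of 3.00/2.8016 = 1.07 and a half-width of 1.96 × 1.07 = 2.1 percentage points, so even an estimate of zero would fail the rule.

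**Conclusion.** The point holds as a matter of wording. The 80% thresholds are about 3.0%/year for admissions and about 4.8–5.2%/year for crime. Most of the quoted admissions interval, including the prior estimate, therefore falls short of 80% power, as does roughly the lower half of the 4–6% crime range: (4.8 − 4)/2 = 40% to (5.2 − 4)/2 = 60% of it.

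The admissions figures rest only on Table 4's inputs and barely depend on the schedule. The crime figures rest on the unstated number of time points, which is why they are given as ranges. All the figures take the variances borrowed from the earlier studies as correct for this one.

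**What to change.** Replace the closing sentence of the Power calculations section with:

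> With 20 areas per group the study has 80% power for slope differences of at least about 3.0%/year for admissions and about 4.8–5.2%/year for crime, depending on the number of time points assumed. Power is about 57–59% at the prior admissions estimate of 2.31%/year (about 46–47% at 2%/year) and about 57–64% at a crime effect of 4%/year.

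If the authors state the number of time points they used, the crime ranges can become single values. In the Discussion, add that a null result should be read with its confidence interval and in light of this power, without a fixed exclusion margin. Check the printed slope in the 5% crime row at the same time.

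The cost is a few sentences. The stated power becomes less favourable; the design, the analysis and the number of areas stay as they are.
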